## Abstract

**Background:**

Total knee replacement (TKR) is one of the most commonly performed routine procedures in the world. Prognostic studies indicate that the number of TKR will further increase constituting growing burden on healthcare systems. There is also substantial regional heterogeneity in TKR rates within and between countries. Despite the known therapeutic effects, a subset of patients undergoing TKR does not benefit from the procedure as intended. To improve the appropriateness of TKR indication, the EKIT initiative (“evidence and consensus based indication critera for total arthroplasty”) developed a clinical guideline for Germany on the indication of TKR. This guideline is the basis for a digital medical decision aid (EKIT tool) to facilitate shared decision making (SDM) in order to improve decision quality for elective surgery. The aim of this cluster randomized trial is to investigate the effectiveness of the EKIT tool on decision quality.

**Methods:**

The Value-based TKR study is a prospective pragmatic multi-center, stepped wedge, cluster randomized controlled trial (SW-RCT). The EKIT tool provides (1) a systematic presentation of individual patient and disease-specific information (symptoms, expectations), (2) the fulfillment of the indication criteria and (3) health information about safety and effectiveness of TKR. All study sites will follow routine care as control clusters until the start of the intervention. In total, there will be 10 clusters (study sites) and 6 sequential steps over 16 month, with clusters receiving the intervention with a minimum 2 months of standard routine care. The primary outcome is patients’ decision quality measured with the Decision Quality Instrument (DQI)-Knee Osteoarthritis questionnaire. Furthermore, we will collect information on global patient satisfaction, patient reported outcome measures and the fulfilment of the individual expectations 12 months after SDM. The power calculation yielded an estimated power of 89% using robust Poisson regression under the following assumptions: 10 study sites with a total of N=1,080 patients (including a dropout rate of 11%), a 10% increase in decision quality due to the use of the EKIT tool, and a significance level of 5%.

**Discussion:**

There is a high potential for transferring the intervention into routine practice if the evaluation is positive.

**Trial registration:**

ClinicalTrials.gov: NCT04837053. Registered on 08/04/2021.

## Background

Knee osteoarthritis (OA), the most common joint disease in the world, is estimated to affect more than 650 million people [1, 2]. It is one of the most common causes of pain and disability in older people [3]. There is currently no causal drug therapy for knee OA [4]. However, for end-stage osteoarthritis, elective joint replacement surgery is a cost-effective treatment option [5, 6]. Total joint replacement (TJR) is one of the most commonly performed routine procedures in the world [7]. There is, however, substantial regional heterogeneity in total knee replacements (TKR) rates within and between countries [6, 8–10]. Based on the demographic change, a further increase in the number of TKR can be assumed [9], which might additionally further increase the heterogeneity of care. Prognoses impressively show the future significant impact on the health care system [11–18]. This is reflected in expected cost increases, but also in increased demand for resources from providers.

Despite the known therapeutic effects, such as pain reduction [6, 19], improvement of function [19–21] and health related quality of life [21–23], a subset of patients undergoing TKR does not benefit from the procedure as intended: (1) the proportion of patients with (residual) pain in the long-term course has been reported between 10 and 34 % [24], (2) residual symptoms and functional limitations between 33 and 54 % [25] and (3) the proportion of patients which are not satisfied has been reported recently still between 12 and 15 % [24, 26]. It was shown that patients whose expectations were fulfilled were also more satisfied with the outcome than those whose expectations were not or only insufficiently fulfilled [27–29]. It has been demonstrated that expectations were modifiable [30]. Consequently, the knowledge of the patient's expectations and treatment goals is necessary for (1) predicting treatment outcomes and, subsequently, for (2) patient-centered indications for elective surgery. Furthermore, these expectations on the surgery should be considered in (3) shared decision making (SDM) in order to address any unrealistic treatment goal and to adjust the therapy or the expectation accordingly.

Standardized assessment of patient and physician expectations related to elective surgery led to more effective consideration of patient goals in the decision making process [31]. Another positive aspect of the standardized collection of patient expectations and treatment goals is the possible individualization of treatment options according to the patient's preferences and needs.

Internationally, the review of Gademan et al [32] summarized the current state of science for the indication for TKR. This overview identified six guidelines for TKR. However, consideration of patient expectations was not included in the recommendations. Therefore, the EKIT initiative (“evidence and consensus based indication criteria for total arthroplasty”) developed a clinical guideline for Germany on the indication of TKR considering treatment goals and the associated probability of achievement [33]. This formed the basis for the idea developing a digital medical decision aid (EKIT tool) that facilitates SDM incorporating patient`s symptoms, expectations and the guideline for physicians aiming to improve decision quality. Overall, medical decision aids can be used as tool for structured SDM [34] and facilitate the communication in the decision-making process [35]. Ideally, the medical decision aids will help to increase the quality of decision-making for both physicians and patients. However, to the best of our knowledge, there is a lack of studies on SDM tools that interact between both physician and patient [36].

Therefore, the aim of this cluster randomized trial is to investigate the effectiveness of the EKIT tool to improve decision quality of the patients. The tool will provide physicians with information about patient-specific and disease-specific factors (predictors) as well as treatment goals and patient preferences (desired outcome) for indication and subsequently visualizes health information for a guided SDM.

## Methods / Design

The SPIRIT (Standard Protocol Items for Randomized Trials) [37], the SPIRIT extension for Patient-Reported Outcomes [38] and SUNDAE (Standards for Universal Reporting of Decision Aid Evaluations) recommendations [39] were used during the whole process of protocol development. Additionally, we followed the extension for stepped wedge cluster randomized trials of the CONSORT (Consolidated Standards of Reporting Trials) statement [40] as supplement for reporting the study design. This trial was registered on ClinicalTrials.gov (NCT04837053, 08/04/2021).

### Study design

The Value-based TKR study is a prospective pragmatic multi-center, stepped wedge, cluster randomized controlled trial (SW-RCT). Each cluster will be randomly assigned to interventions on a staged schedule. In total, there will be 10 clusters (study sites) which will change from control (routine care) to the intervention (EKIT tool) in a predefined randomly allocated sequence. Each cluster will have a minimum 2 months of routine care before changing to the intervention (Fig. 1). At the end of the study, all clusters will be assigned to the intervention with a minimum of 4 months. The total duration of study will be 16 months.

**Fig. 1 Fig1:**
[figure not shown]
The stepped wedge design as applied in Value-based TKR

The rationale behind the design selection was (1) to avoid influencing routine care with knowledge of the intervention, (2) to deploy the digital intervention at the cluster level, as the study intervention should be integrated into routine care, (3) the intention to leave the intervention in place at the end of the study and (4) facilitates cluster recruitment as it enhances the acceptability.

### Study aims

The purpose of this study is (1) to compare the effectiveness of the EKIT tool versus routine care in terms of decision quality and satisfaction with the SDM. Furthermore, we aim to (2) investigate with a 12-month follow-up the impact of the EKIT tool on treatment choices, patient reported outcomes measures (PROM) and satisfaction with treatment outcome. (3) We aim to investigate associations that influence the decision quality on patient and intervention level. Specific study hypotheses are:
*Hypothesis 1*: Patients receiving the intervention have higher decision quality than patients receiving routine care.*Hypothesis 2*.1: Patients report higher satisfaction with the SDM when the EKIT tool was used.*Hypothesis 2*.2: Physicians report higher satisfaction with the SDM when the EKIT tool was used.*Hypothesis 3.1:* After 12 months, patients are more satisfied with their chosen therapy if the EKIT tool was used.*Hypothesis 3.2:* After 12 months, patients are more satisfied with the treatment decision made if the EKIT tool was used.*Hypothesis 3.3:* After 12 months, individual patient expectations are more likely fulfilled if the EKIT tool was used.

### Participants, interventions, and outcomes

#### Study setting

The study will take place in ten surgical centers (study sites) in Germany. During routine care, patients are referred to a surgical center by their outpatient primary care physician or orthopedic specialist for a TKR. Study sites will be chosen from different level of care and infrastructural regions in Germany.

#### Eligibility criteria

##### Cluster inclusion criteria for SW-RCT

Study sites will be included if there is a high probability that the needed sample size may be recruited. Therefore, the volume of at least 200 primary TKR’s per year was required.

##### Patient inclusion criteria for SW-RCT

The target population includes all patients with knee osteoarthritis which are referred for TKR by the treating physician. Eligibility criteria are: (1) patient with knee osteoarthritis who is a candidate for total knee replacement, (2) capacity to consent, (3) understanding of the German language (written and oral), (4) age of 18 years or older, and (5) informed consent. Patients with already performed knee replacement ipsilateral will be excluded from the study.

#### Interventions

##### Intervention cluster - EKIT tool

The intervention (EKIT tool) consists of three parts (Fig. 2). (1) To guide the SDM process and to support the consultation, the EKIT tool provides a systematic presentation of individual patient and disease-specific information and (2) it visualizes the fulfillment of the indication criteria in Germany. (3) To empower the patient, the EKIT tool additionally presents health information about TKR adopted from the health information developed by the German independent Institute for Quality and Efficiency in Health Care (Institut für Qualität und Wirtschaftlichkeit im Gesundheitswesen, IQWIG).
Individual patient information

**Fig. 2 Fig2:**
[figure not shown]
Flow of study intervention and assessment

In addition to the visualization of clinically assessed parameters (e.g. the individual Oxford Knee Score (OKS) in comparison to the OKS distribution before TKR), the EKIT tool presents the expectations and the associated probabilities of fulfillment as estimated by the physician. This combines patient`s and surgeon`s perspective on the TKR.
(2)Indication criteria for TKR in Germany

The German guideline on TKR indication is available on the website of the Association of the Scientific Medical Societies in Germany (AWMF, https://www.awmf.org/leitlinien/detail/ll/033-052.html) and furthermore published in short form for the German orthopedic community [41] and the conceptual framework with the resulting criteria is also available in English [33]. The EKIT tool visualizes the degree of fulfillment of the guideline recommendations for the indication criteria knee TKR. The following five core indication criteria were agreed within the EKIT panel: (1) intermittent (several times per week) or constant knee pain for at least 3–6 months; (2) radiological confirmation of structural knee damage (osteoarthritis, osteonecrosis); (3) inadequate response to conservative treatment, including pharmacological and non-pharmacological treatment for at least 3–6 months; (4) adverse impact of knee disease on patient’s quality of life for at least 3–6 months; (5) patient-reported suffering/impairment due to knee disease.
(3)Health information about TKR

The health information adapted from the IQWIG describes the frequency of adverse events, return to activities and the potential of TKR to reduce discomfort and pain.

##### Control cluster

All study sites will follow routine care as control clusters until the start of the intervention. However, there are additional study –specific data collection processes besides routine care. This deviation from the routine care for participating study sites is necessary to evaluate the effectiveness of the intervention. We have made every effort to keep potential bias to a minimum. The additional data collection includes sociodemographic data, PROM, treatment goals, clinician-based outcomes, information about decision-making, patient participation, and previous therapies (Table 1).

**Table 1 Tab1:** Summary of outcomes, measurement instruments and time of measurement

Outcome Domain	Measurement instrument	Source	Assessor perspective		Study period						Data type
			Patient	Clinician	Enrolment	Pre-Visit (t_**0**_)	Visit (t_**1**_)	Post-Visit (t_**2**_)	Follow-up (t_**3**_)	Close-out	
**Enrolment**											
Eligibility screen					x						**-**
Informed consent					x						**-**
**Intervention**											
Decision aid							x				**-**
Routine care							x				**-**
**Assessments**											
Sociodemographic data											
Sociodemographic	Sociodemographic questionnaire	Self-made				x					-
PROM											
Pain & function	Oxford Knee Score (OKS)	[42]	x			x			x		con (0-48)
Generic health related quality of life	EQ-5D-5l	[43]	x			x			x		con (0-1)
Subjective suffering, health related quality of life, pain	Numeric rating scale (0-10)	Self-made	x			x			x		con (0-10)
Pain	Patient survey	Self-made	x			x			x		cat
Muscoloscleral complaints	Musculoskeletale morbidities	Self-made	x			x			x		cat
Global treatment outcome	5-point Likert-scale	[44]	x						x		cat
Disease-related Symptoms, complaints disabilities	3-point Likert-scale	Self-made	x			x			x		cat
Treatment goals											
Expectations	3-point Likert-scale	Self-made, [45]	x			x					cat
Fullfilment of expectation	5-point Likert-scale	Self-made	x						x		cat
Estimation of the probability of fulfillment	5-point Likert-scale	Self-made, [45]		x		x					cat
CBO											
Range of motion	Angular measurement			x				x^b^			con
Stability	Joint clearance : Mediolateral and anteroposterior			x				x^b^			cat
BMI	Weight and length measurement		x					x^b^			con
Morbidity	Anamnesis			x				x^b^			cat
Contraindication	Anamnesis			x				x^b^			cat
Degree of Osteoarthritis	Kallgren & Lawrence			x				x^b^			cat
Joint space narrowing	X-ray			x				x^b^			cat
Leg axis position	X-ray			x				x^b^			cat
Decision making and patient participation											
Participation in therapy decision	PEF–FB-9	[46]	x					x			con (0-100)
Preference for involvement in decision-making	Control Preferences Scale (CPS)	[47]	x			x					cat
Decision quality	DQI-Knee Osteoarthritis^a^	[48]	x					x	x		cat
	Decision Process Score of the DQI-Knee Osteoarthritis^a^	[48]	x					x			con (0-100)
	4-point Likert Scare	Selfmade				x		x			cat
Decision regret	Decision Regret Scale (DRS)	[49]	x						x		con (0-100)
Satisfaction with consultation (physician)	5-point Likert-scale	Self-made	x					x			cat
Satisfaction with consultation (patient)	5-point Likert-scale	Self-made		x				x			cat
Agreed medical treatment decision	NA	Self-made		x				x			cat
Adherence to clinical guideline	Fulfillment of indication criteria	Self-made		x				x	x		cat
Previous therapy											
Conservative therapy	Patient survey	Self-made	x			x			x		-
Operative therapy	Patient survey	Self-made	x			x					-

^a^ Modified version of the DQI- Knie; PROM: Patient reported outcome measure; CBO: Clinician-based outcome; Categorial (cat); Continuous (con) ^b^ in the intervention group during counseling

#### Outcomes

##### Primary outcome

The primary outcome for this trial is the patient’s decision quality after the patient-physician consultation. The binary outcome of the informed patient-centered decision will be measured with the Decision Quality Instrument (DQI)-Knee Osteoarthritis [48] questionnaire and reflects the extent that patients are informed (at least three out of five knowledge questions are correct, ≥ 60% in the knowledge score) and receive their preferred treatment (conservative vs. TKR). In detail, the proportion of right answers of the five item knowledge questionnaire are scored on a scale ranging from 0% to 100%. To obtain concordance between preferences and treatment received, the patient is asked about the preferred treatment immediately after the consultation (t_2_) and the treatment received is reported within the follow-up 12 months after the consultation (t_3_). Finally, an informed patient-centered decision is present if the individual knowledge score is ≥ 60% and the preferred and received treatment are concordant. The primary analysis examines differences between intervention and control regarding the probability of informed patient-centered decisions.

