##### Confirmatory analysis

The confirmatory analysis of the primary outcome (decision quality, DQI-Knee Osteoarthritis) [48] is performed as complete case-analysis by estimating the effect of EKIT tool implementation on decision quality using robust Poisson regression for clustered data [52]. The use of this method allows direct estimation of the relative increase in the probability of good decision quality while adequately accounting for the data structure. Furthermore, a regression-based approach allows adjustment for other relevant covariates in the context of sensitivity analyses. Interim analyses were not planned in this study.

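### Defining concordance by the treatment received at 12 months scores informed patients still waiting for an agreed TKR as failures, which lets operating capacity into the primary outcome

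*Protocol article*

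**What the plan says.** The section Primary outcome of the protocol article opens: "The primary outcome for this trial is the patient’s decision quality after the patient-physician consultation". The scoring rule is: "an informed patient-centered decision is present if the individual knowledge score is ≥ 60% and the preferred and received treatment are concordant". Knowledge and preference are taken at t2, directly after the visit. The other half of the concordance comparison comes a year later: "the treatment received is reported within the follow-up 12 months after the consultation". The treatments compared are conservative care and TKR.

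Table 1 also lists an item called "Agreed medical treatment decision", reported by the clinician at t2. The primary outcome does not use it.

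The section Confirmatory analysis names a complete-case robust Poisson regression for clustered data. It names no calendar-time term, and says of the regression approach that it "allows adjustment for other relevant covariates in the context of sensitivity analyses". Under Methodological considerations, the article accepts that secular trends can bias a stepped wedge design but expects little effect, because nothing is known about such trends for these outcomes.

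**The concern.** The outcome is described as a property of the decision, but its value also depends on whether the operation took place within a year. Take a patient who passes the knowledge threshold, prefers TKR and agrees TKR with the surgeon. If the operation is still pending at t3, the patient has not received the preferred treatment and is scored as a failure. The decision was the same as that of a patient operated on in month 11. What differs is the waiting list, which the tool does not target.

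The design makes this more than noise. Each site starts in control and ends in intervention, so intervention patients are enrolled later on average. If the share still waiting at 12 months changes over the recruitment period, the change lines up with the tool. A model without calendar time would credit it to the tool or hold it against it.

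**Working it through.** **Inputs from the article.** Control rate 44.5%; 10% increase; N = 1,080 with 11% dropout, so 1,080 × 0.89 ≈ 961 evaluable; random-intercept SD 0.01; significance level 5%; stated power 89%; 10 sites, 6 steps, 16 months, at least 2 months of control and 4 of intervention per site.

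**Assumptions.** Switch months 2, 4, 6, 8, 10 and 12, because Fig. 1 is not shown; a two-sided test; waiting shares between 0% and 30%, because the documents give none. The share w is applied to all patients who would otherwise be successes. Simulations used 2,000 runs per setting: logistic data generation, then Poisson regression with a log link and sandwich variance.

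**1. The stated power.** With an absolute increase from 44.5% to 54.5% and no time term, simulated power is 0.88–0.90 with 1,080 analysed and 0.84–0.88 with 961, depending on the layout. The stated 89% is therefore reproduced. A relative 10% increase (to 48.95%) gives only 0.24–0.36. With a linear time term or 2-month periods, power is about 0.50–0.65. The stated figure thus fits a model without calendar time.

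**2. Constant waiting share, w = 10%.**
- Control: 0.445 × 0.90 = 0.4005. Intervention: 0.545 × 0.90 = 0.4905.
- Risk ratio: 0.4905 / 0.4005 = 1.225 = 0.545 / 0.445. The relative effect does not change.
- Simulated power with 961 evaluable falls from 88% to 79%.
- Hand check with 56.25% of patients under intervention (about 420 and 541): without waiting, z = 0.100 / 0.0323 = 3.09, power Φ(3.09 − 1.96) = 0.87. With w = 10%, z = 0.090 / 0.0321 = 2.80, power Φ(2.80 − 1.96) = 0.80.

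**3. Drifting share, no time term, 961 evaluable.** Share moving linearly over the 16 months:

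| Share still waiting, start to end | True tool effect | Estimated RR | Significant results |
|---|---|---|---|
| 20% to 10% | none | 1.06 | 9% |
| 20% to 0% | none | 1.11 | 24% |
| 30% to 10% | none | 1.12 | 26% |
| 10% to 20% | RR 1.225 | 1.16 | 47% |
| 0% to 20% | RR 1.225 | 1.11 | 28% |
| 10% to 30% | RR 1.225 | 1.10 | 20% |

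Hand check of the first row: allocate 1, 2, 2, 2, 2 and 1 sites to the six steps. The mean enrolment month is then 4.14 for control and 11.0 for intervention. The share waiting is 20 − 10 × 4.14/16 = 17.4% in control and 20 − 10 × 11.0/16 = 13.1% in intervention. The risk ratio with no tool effect is (1 − 0.131) / (1 − 0.174) = 1.05, in line with the simulated 1.06.

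**4. Same scenarios with calendar time in the model.** The risk ratio with no tool effect returns to 0.99–1.01 and rejections to 4–6% in every scenario, with linear time or 2-month periods. Power with linear time is about 55% without waiting and 40–50% in the waiting scenarios.

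**The case against.** The strongest reply is that the article never mentions a patient whose surgery is pending. The t3 form, the modified questionnaire and any SAP are not shown and might separate performed from scheduled operations. That is possible, but the rule as printed compares preference with treatment received, and a patient awaiting surgery has not received it. The consequence follows from the stated definition unless another document overrides it.

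A second reply is that receiving the preferred treatment is a legitimate, prespecified construct. This stands, and it is why the primary outcome should be kept.

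A third is that the bias is a case of general time-trend confounding, not a fault of the outcome alone. This also stands: step 4 shows that a calendar-time term removes a drift common to all sites. The bias needs the received-treatment rule and an unadjusted model together. If an SAP already adjusts for time, only the power loss and the interpretation remain.

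Three stronger readings are tempting, and the documents do not support them:
- *Undecided patients fit no category and drop out.* The article names two treatments ("receive their preferred treatment (conservative vs. TKR"), but these are the treatments compared, not shown response options. The modified questionnaire may force a choice or carry its own scoring rule.
- *A stable waiting share dilutes the primary effect.* The planned estimate is relative, and step 2 shows it unchanged. Only the absolute difference and the power shrink.
- *Waiting could shift the result by four points or more.* Such a figure (0.445 × 0.10 = 4.45 points) needs a 10-point contrast between phase averages. Control and intervention overlap in calendar time. In the layout of the hand check, that contrast would take a drift of 10 / (6.86/16) ≈ 23 points within 16 months.

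Patients who prefer conservative care cannot be waiting. A given w across all would-be successes therefore implies a higher share among those who prefer TKR.

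**Conclusion.** The point holds in a limited form. On its plain reading, the primary outcome counts informed patients with an agreed but pending TKR as failures, provided they return the t3 questionnaire. Non-responders leave the complete-case analysis. An outcome presented as decision quality after the consultation therefore partly reflects surgical capacity.

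A stable share costs power only: about 9 percentage points at an assumed 10%. A drifting share would bias the estimate in either direction under a model without calendar time: RR about 1.06 and 9% rejections for a tool with no effect under an assumed fall from 20% to 10%, with larger errors for steeper drifts. These sizes rest on assumed waiting shares, an assumed step layout and 961 evaluable patients. A reader might infer that the trial result will be biased. The documents give no waiting times, so neither the existence nor the direction of a drift can be shown.

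**What to change.** Leave the definition of the primary outcome as it is, and make three additions before analysis.

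1. Prespecify a sensitivity analysis in which concordance means that the preference at t2 matches the agreed treatment decision at t2. Both are collected, so no new data are needed. Waiting lists and non-return of the t3 questionnaire do not affect it. Its weakness is that the clinician reports the agreed decision from the same unblinded visit, and it may match the patient's preference almost automatically. It can support the primary analysis but not replace it.
2. At t3, record whether a TKR was performed, is scheduled or neither. The primary result can then be repeated with a scheduled TKR counted as concordant with a TKR preference. The cost is one answer option. Because this departs from the strict received-treatment wording, it should remain a sensitivity analysis.
3. Include calendar time in the primary model. This removes a drift common to all sites, whether from waiting or another source. The cost is precision: simulated power falls to about 0.50–0.65 under the article's assumptions, so the stated 89% must be recalculated for the model actually used.
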